## Abstract

**ABSTRACT:**

**Introduction:**

Treatment for women with endometriosis is only partially or temporarily effective. Moreover, medical hormonal treatment is associated with debilitating side effects and interferes with fertility, while surgery has a relatively high risk of complications. Meanwhile, women with endometriosis show increasing interest in implementing lifestyle interventions to alleviate symptoms and improve health-related quality of life (HRQoL). Integrating these lifestyle interventions can provide a holistic approach to the treatment of this debilitating disease. However, scientific evidence supporting the effectiveness of these interventions is limited. This study is designed to investigate the effectiveness of two lifestyle interventions and the combination of both: an anti-inflammatory diet intervention (AIDI) could improve immune cell function and reduce inflammation, resulting in improved HRQoL and alleviating pain. In addition, the integration of cognitive behavioural therapy (CBT) aims to provide insight into pain mechanisms and coping with pain, and to assist in sustaining dietary adjustments.

**Methods and analysis:**

The Pain in Endometriosis And the Relation to Lifestyle (PEARL) study is a five-arm randomised controlled trial with a pre-post factorial design with two factors: an AIDI and CBT. The study population will consist of 250 premenopausal women, of whom 200 are diagnosed with endometriosis and experience pain symptoms and 50 are healthy controls (HC). Women with endometriosis will be recruited from one academic tertiary and five secondary hospitals in the Netherlands. They will be randomised (1:1:1:1) among four intervention groups: standard care (SC) (SC group), SC and an AIDI (SC + AIDI group), SC and CBT (SC + CBT group), and SC, AIDI and CBT (SC + AIDI + CBT group). Women with endometriosis will visit the hospital twice during the intervention period, at the start (T0) and end (T2) of the 13-week intervention period. HC will not undergo any of the interventions and will have one hospital visit (T0). Participants will complete questionnaires regarding pain symptoms, HRQoL, physical activity level, sleep, diet quality, pain cognitions, and stress at T0 and T2. Furthermore, they are instructed to collect menstrual effluent, a vaginal swab and a faecal sample. During the study visits, peripheral blood will be drawn and scalp hair samples will be taken. The primary outcome is average pain, measured using a numerical rating scale. Secondary outcomes focus on HRQoL, inflammation, immune system characteristics, vaginal- and gut microbiome, and hair cortisol levels. These are considered to reflect potentially underlying mechanisms of the effect of both interventions on the primary outcome. Biological samples and questionnaires of women with endometriosis and HC will be compared to establish the differences in secondary outcomes.

**Ethics and dissemination:**

This study protocol has been approved (approval number: NL86247.091.24) by the METC Oost-Nederland from Radboud University Medical Centre on July 11, 2024. Prior to participation, participants are required to provide informed consent. The results will be widely disseminated through scientific peer-reviewed journals, and presentation to a broad audience in scientific meetings, congresses, patient meetings, as well as in policy-relevant forums.

**Trial registration number:**

NCT06332560.

STRENGTHS AND LIMITATIONS OF THIS STUDYThe combination of two lifestyle interventions, an anti-inflammatory diet intervention (AIDI) and cognitive behavioural therapy (CBT), is an innovative approach.The AIDI and CBT protocol were carefully designed by a team of dietitians and psychologists, and will be personalised, which will improve the adherence to the intervention as well as its effect.The integrative approach of objective and subjective data will offer insights into both biological and psychological mechanisms affecting endometriosis.Due to the nature of the interventions, participants cannot be blinded to group allocation.As the AIDI and CBT are personalised, the intervention is not completely standardised.

## Introduction

 Many individuals diagnosed with endometriosis continue to experience recurrent symptoms even after undergoing surgery or using hormonal suppression.^1^ Despite being the most prevalent benign gynaecological disorder, affecting approximately 10% of reproductive age individuals (from here referred to as reproductive age women), endometriosis cannot be cured to this day.^1 2^ Therefore, self-management strategies such as lifestyle interventions become vital for long-term alleviating symptoms and improving health-related quality of life (HRQoL). These strategies can empower women with endometriosis to actively manage their symptoms, fostering greater autonomy and resilience.^3^ Ultimately, integrating these lifestyle interventions in the treatment of endometriosis provides a holistic approach in the managment of this debilitating disease.

Endometriosis is a chronic, oestrogen-dependent inflammatory disease characterised by the presence of endometrial-like tissue outside the uterine cavity.^1^ Mounting evidence implicates immune dysregulation and persistent inflammation in the pathophysiology and severity of symptoms.^4^,^7^ Endometriotic lesions recruit a large number and diversity of immune cells which contributes to increased production of cytokines, chemokines and growth factors. This results in an enhanced inflammatory environment in the peritoneal cavity.^8^ Furthermore, elevated oestradiol levels in endometriotic lesions further exacerbate the inflammatory environment.^9^ This inflammatory reaction stimulates the activity of nerve fibres in and around the endometriotic lesions, which eventually leads to peripheral sensitisation. In the long term, this may result in changes in the central nervous system leading to heightened pain perception, known as central sensitisation, potentially contributing to chronic pelvic pain,^10^ the hallmark symptom of endometriosis.^11^ Furthermore, endometriosis can present with dysmenorrhoea, dyspareunia, dysuria and dyschezia, as well as gastrointestinal symptoms, infertility, migraine, and fatigue.^12 13^ Besides the physical symptoms associated with endometriosis, this condition can also affect psychological well-being and impair economic productivity and social relationships, which negatively affects HRQoL.^14^,^16^

To alleviate pain symptoms and improve HRQoL, many women with endometriosis turn to self-management strategies. While dietary adjustments have been identified as one of the most used self-management strategies in reducing pelvic pain and gastrointestinal symptoms by women with endometriosis,^3^ there is no specific diet that consistently proves to alleviate symptoms more effectively than other dietary interventions.^17^ Furthermore, the scientific evidence regarding the effectiveness of dietary interventions remains of low quality, with a lack of large-scale intervention studies investigating the effect of these dietary interventions on endometriosis-related pain symptoms and HRQoL.^18^ In addition, it is unclear whether the experienced symptom reduction is attributable due to the self-empowerment effect^19 20^ or because pain symptoms may be alleviated due to a biological mechanism of nutrition on the body.

Several macro- and micronutrients have been shown to influence the immune status of an individual.^21 22^ A person’s inflammatory status can switch from pro- to anti-inflammatory. The Western diet, which is typically rich in processed foods, refined sugars, saturated fats, trans fats, and low in dietary fibre, is associated with immune dysregulation and low-grade chronic inflammation. In contrast, a diet rich in anti-inflammatory nutrients such as antioxidants, dietary fibre and omega-3 fatty acids from vegetables, fruits, whole grains, legumes, nuts, fatty fish, and olive oil is associated with beneficial effects on the immune system and reduced inflammatory responses.^23 24^ Therefore, an anti-inflammatory diet intervention (AIDI) may be effective in influencing the inflammatory status of women with endometriosis, resulting in the suppression of pain symptoms.

Similar to the biological and physical determinants of pain, psychological factors also contribute significantly to its experience,^25^ they play a crucial role in pain perception, often even surpassing the impact of physical symptoms. Women with endometriosis are prone to exhibit negative pain cognitions, including catastrophising and hypervigilance, which independently influence HRQoL.^26^ Furthermore, endometriosis is associated with increased stress levels. The relationship between stress and endometriosis is bidirectional, as, next to endometriosis leading to elevated stress levels, stress itself can exacerbate symptoms and disease progression.^27^ Stress and pain intensity are positively correlated; women with endometriosis reporting high stress levels exhibit significantly higher pain scores. Positive coping strategies are associated with better stress adaptation. Understanding the psychological aspects of pain can help women with endometriosis participate in their own pain management and assist clinicians in creating supportive environments for treatment.^28^ Cognitive behavioural therapy (CBT) is a psychological intervention which is proven effective in other chronic pain conditions and targets to help identify, modify and reduce negative cognitions and behaviours, which can help to decrease pain catastrophising, hypervigilance and anxiety.^29 30^

Thus, supporting women with endometriosis through lifestyle interventions may be crucial for symptom management and improving HRQoL. Therefore, the Pain in Endometriosis And the Relation to Lifestyle (PEARL) study examines the effects of two lifestyle interventions: an AIDI and CBT, on endometriosis-related symptoms and HRQoL. Both interventions are tested separately, as well as in conjunction with one another, to examine whether the combination of these interventions has an enhancing effect. To explore a possible underlying biological mechanism as a contributing factor for symptom improvement, the gut and vaginal microbiome, hair cortisol levels, inflammatory markers and immune cell composition in peripheral blood (PB), and menstrual effluent (ME) are being analysed before and after the interventions. In addition, this study aims to identify differences in these biomarkers between women with and without endometriosis to gain a deeper understanding of the pathogenesis of endometriosis. We assume that this will contribute to new insights in diagnostics and potential new treatment strategies for women with endometriosis.

## Methods and analysis

### Study design

This is a study protocol for a randomised controlled trial (RCT) with a pre-post factorial design with two factors: an AIDI and CBT. Women with and without endometriosis will be included, resulting in an RCT with five arms. Women with endometriosis will be randomised among four arms: a control group receiving standard care (SC group) and three intervention groups: receiving standard care and adhering to an AIDI (SC + AIDI group), receiving standard care + CBT (SC + CBT group), and receiving standard care, adhering to an AIDI, and receiving CBT (SC + AIDI + CBT group). The fifth arm is allocated to serve as the healthy control (HC) group (women without endometriosis diagnosis). HCs will not receive any of the interventions. An overview of the study design is presented in figure 1. This protocol was developed in accordance with the Standard Protocol Items: Recommendations for Interventional Trials reporting guidelines.^31^

**Figure 1 F1:**
[figure not shown]
Overview of the study design. AIDI, anti-inflammatory diet intervention; CBT, cognitive behavioural therapy; CIS, Checklist Individual Strength; CSI, Central Sensitisation Inventory; EHP-30, Endometriosis Health Profile-30; FFQ, food frequency questionnaire; IPAQ-SF, International Physical Activity Questionnaire Short Form; NRS, Numerical Rating Scale; PASS, Pain Anxiety Symptom Scale; PSC, Pain Catastrophising Scale; PSQI, Pittsburgh Sleep Quality Index; PSS, Perceived Stress Scale; SC, standard care; SF-36, Short Form Healthy Survey-36.

### Patient and public involvement

Prior to the development of this study protocol, we conducted two qualitative studies in which the feasibility of an AIDI and CBT for women with endometriosis was identified.^32 33^ Information acquired in these studies was taken into account when designing both interventions used for this study protocol. In addition, members of endometriosis patient organisations from the Netherlands (‘the Dutch Endometriosis Society’), Croatia (‘I am 1 in 10’) and the UK (‘Endometriosis UK’) were involved in the development of this study protocol.

### Sample size calculation

The calculation of the required sample size for this RCT was conducted for the primary outcome, average pain intensity measured with a Numerical Rating Scale (NRS). Based on preliminary results of our single-arm explorative feasibility study and the RCT of Field *et al*, where a whole-food diet was implemented that restricts ultra-processed foods for pain management in chronic pain patients,^34^ we assume a pre-post correlation of r = 0.3. Although the single-arm trial found an effect (pre-post) of 1 SD, the expected effect size was set at 0.6 SD (–1.14).

For the CBT no pilot data were available. Therefore, the calculation of the effect size for this intervention was based on an RCT describing the efficacy of CBT in enhancing coping strategies, alleviating depression, stress, pain perception and improving the quality of life for women with endometriosis.^35^ In this study an effect of 0.55 SD was observed. For the current RCT this would translate to a similar effect of CBT as of the AIDI, so −1.14. We assume that the pre-post SD σ and correlation will be the same for all arms.

With 40 participants per arm, the precision for the main effects of AIDI and CBT yields an SD of 0.405, providing power greater than 80% for detecting an effect size of 1.14. However, the interaction effect has an SE of 0.57, ie, with a 95% CI for the estimated difference of ±1.12. This allows to observe an interaction effect in the order of magnitude of AIDI and CBT effects.

Based on our pilot-study we expect a dropout rate of 20–25%. Therefore, ten additional participants will be included in each arm of the RCT, resulting in a target sample size of 50 participants per arm, in total 200 women with endometriosis.

The evaluation of differences between HCs and women with endometriosis will be an explorative part of the study to generate preliminary insights. In the literature a sample size of 30–50 is described as a reasonable minimum sample size.^36^ Considering the potential drop-out and the group size in the other arms of the RCT, the total sample size for this RCT will be 250, of which 200 will be women diagnosed with endometriosis and 50 HC women.

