### Statistical analysis

Data collected via questionnaires will be analysed using the software IBM SPSS V.29 for Microsoft Windows, data regarding the biological samples will be analysed using R software. The threshold for statistical significance is defined as <0.05.

For the primary outcome, pain NRS scores, repeated measures ANOVA will be conducted with time (T0 vs T2) as the within-participants variable, group (SC, SC + AIDI, SC + CBT, and SC + AIDI + CBT) as between-participant variable, and the pain NRS score as the dependent variable. If there are missing data, or a temporary study halt, a linear mixed model will be used instead of repeated measures ANOVA. Model fit will be assessed with residuals vs predicted plots and observed vs predicted plots. An intention-to-treat analysis will be followed in the case of follow-up losses. In this analysis, participants are analysed according to their original group assignment, regardless of whether they completed the treatment or dropped out, to minimise the risk of bias due to selective dropout. Given the random assignment of the intervention groups, a regression analysis on the pre-post change, adjusting for the pre-intervention score will be used to measure the main effect of the AIDI and CBT, and estimate interaction effects. Mediation analysis will be conducted to understand if and how secondary outcome measures mediate the effect of the intervention on the primary outcome.

To investigate the differences between women with and without endometriosis at baseline, a Welch’s ANOVA will be performed. This method is chosen to account for unequal group sizes and variances. In case the data are not normally distributed, a non-parametric Kruskal-Wallis test will be used.

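### The power statement does not agree with its own inputs: 0.55 SD for CBT is about -1.05, not -1.14; 50 per arm leaves 40 only at 20% dropout; and 0.405 is the standard error of a single-arm contrast, not of the factorial main effect

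*Protocol article*

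**What the plan says.** All the figures stand in the section on sample size calculation of the protocol article.

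- For AIDI, "the expected effect size was set at 0.6 SD", equated with -1.14 NRS points.
- For CBT, with reference to an external trial, "In this study an effect of 0.55 SD was observed". The next sentence says that "this would translate to a similar effect of CBT as of the AIDI", and gives -1.14 again.
- On variability, "We assume that the pre-post SD σ and correlation will be the same for all arms"; and "we assume a pre-post correlation of r = 0.3".
- With 40 per arm, a precision of 0.405 (printed as an SD) is given for the main effects of AIDI and CBT, with power above 80% for 1.14. The interaction has a standard error of 0.57 and a 95% confidence interval of ±1.12.
- Expected dropout is 20-25%, and so "ten additional participants will be included in each arm of the RCT", giving 50 per arm and 200 in total.

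The statistical analysis section names a regression of the change score, adjusted for baseline, for the two main effects and the interaction. On the error rate it says only "The threshold for statistical significance is defined as <0.05".

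**The concern.** The section makes one power claim for two interventions, and three of its inputs do not fit together.

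1. The section implies a single SD for all arms. On that SD the cited CBT effect is smaller than the one used, and the only reason given is that the effects are similar.
2. The dropout allowance covers the lower end of the stated range and not the upper end.
3. The precision is labelled as that of the main effects but has the size expected when one arm is compared with another.

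The first two matter because the power on the printed precision has no room for either. The third decides how much they matter. A null CBT result will be read against the stated power, so the reader needs to know which comparison that power belongs to.

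**Working it through.** **Inputs** (all from the sample size section unless noted): AIDI effect 0.6 SD = 1.14; CBT source effect 0.55 SD; common SD and pre-post correlation, r = 0.3; 40 evaluable and 50 enrolled per arm; dropout 20-25%; baseline-adjusted regression (statistical analysis section). Two-sided alpha of 0.05 is assumed, since sidedness is not stated; the printed ±1.12 fits it.

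**Step 1: reproduce the plan's figures.**

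- Implied SD = 1.14 / 0.6 = 1.90.
- Residual SD after baseline adjustment = 1.90 x √(1 - 0.3²) = 1.8125.
- 40 vs 40: SE = 1.8125 x √(2/40) = 0.4053. This is the printed 0.405.
- Interaction: SE = 1.8125 x √(4/40) = 0.573, and 1.96 x 0.573 = 1.12. These are the printed 0.57 and ±1.12.
- Power at 1.14 = Φ(1.14/0.4053 - 1.96) = 80.3% (79.8% with the noncentral t distribution).

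Other readings do not give 0.405. An unadjusted change score gives 0.503 for 40 vs 40 and 0.355 for 80 vs 80. A post-only comparison gives 0.425 and 0.300.

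**Step 2: the main effect of a 2x2 design.** Each factor is compared over two arms against two arms, 80 vs 80: SE = 1.8125 x √(2/80) = 0.287. So 0.405 is the SE of a simple effect, for example AIDI alone or CBT alone against SC.

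**Step 3: the CBT effect.** 0.55 x 1.90 = 1.045. The 1.14 used is 1.14 / 1.045 = 1.09 times that, 9% larger. To reach 1.14 from 0.55 SD would take an SD of 1.14 / 0.55 = 2.07.

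**Step 4: dropout.** 50 x 0.80 = 40; 50 x 0.75 = 37.5. Keeping 40 at 25% would take 40 / 0.75 = 53.3, so 54 per arm. Ten is a quarter of 40, but the loss applies to the number enrolled.

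**Step 5: power = Φ(effect/SE - 1.96).**

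| Contrast | Evaluable per arm | SE | AIDI, 1.14 | CBT, 1.045 |
|---|---|---|---|---|
| One arm vs SC | 40 | 0.405 | 80.3% | 73.2% |
| One arm vs SC | 37.5 | 0.419 | 77.7% | 70.4% |
| Pooled main effect | 40 | 0.287 | 97.8% | 95.4% |
| Pooled main effect | 37.5 | 0.296 | 97.1% | 94.2% |

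On an unadjusted change score, which is less efficient, the pooled CBT effect of 1.045 still has 83.6% power at 40 per arm and 81.2% at 37.5.

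**The case against.** The strongest reply is that the protocol names main effects throughout. The study design section describes a two-factor trial, and the statistical analysis section uses regression for the main effects of AIDI and CBT. On that contrast power stays well above 80% with the smaller CBT effect and 25% dropout together. This stands: a reader might infer from 0.405 that the trial is underpowered for CBT, and the documents do not support that as a general statement.

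It does not rescue the printed text, because the only power claim is attached to 0.405. Nor is the single-arm contrast far-fetched. The introduction says the interventions are tested separately as well as together. The analysis includes a four-level group factor. In a dummy-coded model with the interaction, the AIDI and CBT coefficients are simple effects with this SE. In the combined arm each CBT session also deals with adherence to the diet, so an interaction is plausible by design.

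A second reply is that the CBT figure is a planning judgement, not a miscalculation. This also stands in part. The text claims similarity, not an exact conversion, and does not show which SD the external trial used. If its 0.55 were in units of the SD of change (an assumption: 1.90 x √(2 x 0.7) = 2.25), it would be 1.24 points, so 1.14 lies within 1.05-1.24. What remains is that the section states no such basis, assumes one SD for all arms, and rounds 0.55 up to 0.6 without explanation.

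A third reply is that the dropout gap is small and that a linear mixed model is planned for missing data. The gap is indeed 2.5 women per arm. The model cannot restore missing T2 scores, however, and a correlation of 0.3 makes baseline a weak substitute.

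**Conclusion.** The point holds as an inconsistency among the stated effect, standard error, evaluable number and power. On the contrast that 0.405 describes, power is 80.3% at best. It drops to 73% for CBT at 1.045, 78% for AIDI with 37.5 per arm, and 70% for CBT with 37.5 per arm. On the pooled main effect it is 94-95% for CBT and 97-98% for AIDI, so the trial's size is adequate if that contrast is primary.

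Two stronger readings should be avoided: that power fails for CBT outright, and that -1.14 is a proven arithmetic error. The first depends on a choice of contrast that the article leaves unclear. The second depends on a source SD that it does not show.

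The figures rest on two-sided alpha of 0.05, SD 1.90 in every arm, r = 0.3, baseline adjustment, equal dropout across arms and, for the pooled main effect, the stated effect being the average over both levels of the other factor.

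**What to change.** Keep 200 randomised and rewrite the sample size section as follows.

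- Say which contrast 0.405 describes and which contrast is primary, and print the matching standard error: 0.287 for the pooled main effect with 40 per arm, 0.405 for one arm against SC. Call it a standard error.
- State the CBT effect as -1.05 (0.55 SD), or give the reason for -1.14.
- Quote power for AIDI and CBT separately, over 37.5-40 evaluable per arm.

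The cost is a few restated figures and less favourable numbers for the single-arm contrasts. If those were declared primary, 80% power for 1.045 would take 48 evaluable per arm, or 48 / 0.75 = 64 enrolled at 25% dropout. The planned 200 supports the pooled main effects, and the section can say so.

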#### Cognitive behavioural therapy

For the CBT, a protocol has been developed in concordance with several psychologists having affinity with the treatment of women with endometriosis. This protocol is shown in online supplemental table 1. CBT will be provided by a trained psychologist with experience in the treatment of women with endometriosis. During the intervention period there will be in total seven individual CBT sessions. Psychologists will follow the protocol, but the treatment can be personalised based on the results of the PCS and PASS questionnaire. The first CBT session will take 1 hour and will take place face to face in the hospital, subsequent sessions will take approximately 45 min and may be done online.

In the first session, management of expectations towards the CBT (and AIDI) will be addressed. In the six other sessions, attention will be paid to the biological link between endometriosis-related pain and stress, relaxation training, cognitive stress management, sexual relationships, and the management of anxiety, catastrophising, and hypervigilance. When a participant is allocated to the SC + AIDI + CBT group, every CBT session will also focus on how to be able to adhere to the AIDI. In addition to the sessions provided by a psychologist, an online CBT module is available containing general information about psychological mechanisms of chronic pain and exercises on coping with pain in the context of behaviour, cognitions, and emotions. Participants in the SC + CBT and SC + AIDI + CBT group can use this online module freely to re-explore information already explained in the face-to-face sessions.

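### The 0.405 given as the precision of the AIDI and CBT main effects is the standard error of one intervention arm against standard care; the factorial main effect has SE 0.287

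*Protocol article*

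**What the plan says.** The protocol article describes a two-factor (AIDI, CBT) factorial trial with 1:1:1:1 randomisation of women with endometriosis to four arms (Study design; Randomisation).

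Under Sample size calculation, the AIDI effect is set at 0.6 SD, equated to 1.14 NRS points. For CBT the section says: "For the current RCT this would translate to a similar effect of CBT as of the AIDI, so −1.14". It adds "we assume a pre-post correlation of r = 0.3" and "We assume that the pre-post SD σ and correlation will be the same for all arms". It then states that, with 40 women per arm, "the precision for the main effects of AIDI and CBT yields an SD of 0.405, providing power greater than 80" per cent for 1.14. The next sentence gives an interaction SE of 0.57 and a 95% confidence interval of ±1.12.

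Under Statistical analysis, a regression on the pre-post change, adjusted for the baseline score, "will be used to measure the main effect of the AIDI and CBT, and estimate interaction effects".

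**The concern.** In a balanced 2x2 trial, the interaction (a difference of differences) has exactly twice the standard error of a main effect. The two figures printed side by side, 0.57 and 0.405, have a ratio of 1.41. That is the ratio of the interaction to a simple effect, meaning one factor compared at a single level of the other. The figure and its label therefore do not belong together.

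The label matters because the two effects answer different questions. The main effect of AIDI averages over women with and without CBT. The simple effect is AIDI alone against standard care. They coincide only without interaction, and an interaction is plausible here: in the combined arm, "every CBT session will also focus on how to be able to adhere to the AIDI". The power available also differs greatly between the two, so a reader cannot tell from this paragraph which comparison the trial was sized for.

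**Working it through.** **Inputs**
- Effect 1.14 points = 0.6 SD, so the implied SD is 1.14/0.6 = 1.90 (Sample size calculation; the SD itself is not printed).
- Pre-post correlation 0.3, the same SD and correlation in all arms, 40 evaluable per arm (same section).
- Baseline-adjusted regression on change, significance threshold 0.05 (Statistical analysis). Two-sided testing is assumed, in line with the 95% interval.

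**Residual SD after baseline adjustment**
1.90 × √(1 − 0.3²) = 1.90 × √0.91 = 1.8125.

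**Reproducing the plan's figures**
- 40 against 40: 1.8125 × √(1/40 + 1/40) = 0.405, the figure printed for the main effects.
- Interaction, four cells of 40: 1.8125 × √(4/40) = 0.573, half-width 1.96 × 0.573 = 1.12. Both match the text.

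One residual SD thus reproduces all three printed numbers.

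**The factorial main effect**
- 80 against 80: 1.8125 × √(1/80 + 1/80) = 0.287.
- Cross-check: 0.573/2 = 0.287.
- Overstatement: 0.405/0.287 = 1.41, or 41%.
- Other analysis models do not rescue the label. For 80 against 80, an unadjusted change score gives 0.355 and an SD of 1.90 with no adjustment gives 0.300.

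**Power for 1.14** (normal approximation: Φ(1.14/SE − 1.96))

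| Comparison | SE | Power | Detectable at 80% power |
|---|---|---|---|
| Main effect, 80 vs 80 | 0.287 | 97.8% (97.7% by t, 155 df) | 0.80 |
| Single intervention vs SC, 40 vs 40 | 0.405 | 80.3% (79.8% by t, 155 df) | 1.14 |

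**What the main-effect power rests on.** The main effect equals the simple effect plus half the interaction. Two illustrative shortfalls of the combined arm from additivity (assumed sizes, not in the document):
- Shortfall 0.57: main effect 1.14 − 0.285 = 0.855, power Φ(0.855/0.287 − 1.96) ≈ 85%.
- Shortfall 1.14: main effect 1.14 − 0.57 = 0.57, power ≈ 51%.

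**Coding.** In a regression with the interaction term and 40 per cell, 0/1 coding gives coefficient SEs of 0.405, 0.405 and 0.573. Coding centred at ±1/2 gives 0.287, 0.287 and 0.573. The printed figure therefore matches the coefficient that represents a simple effect.

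**The case against.** The strongest reply is that nothing in the trial's size depends on the slip. The text claims only power above 80%. That is true of the main effects by a wide margin if there is no interaction, and by normal approximation it is just true of the single-arm comparison as well. The SE errs in the cautious direction. This stands: a reader might infer that the power claim is false or that 200 women are too few, and the document supports neither.

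A reader might also infer that the analysis will report AIDI alone against standard care under the name of a main effect. The match with a 0/1-coded coefficient invites this, but it shows at most how the number may have arisen. The Statistical analysis section fixes no coding, and in a factorial trial its wording ordinarily means the effect averaged over the other factor. Coding may well be settled in the full protocol or an analysis plan that is not shown. It is a risk to guard against, not a stated error.

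Nor does the attention to diet adherence in the combined arm's CBT sessions establish an interaction. It makes one plausible; the document gives no size for it, and it already plans to estimate it.

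Finally, calling 0.405 an SD is defensible, since the SD of an estimator is its standard error. The inconsistency with the SE in the next sentence is only one of wording.

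None of this removes the wrong figure: 0.405 is not the SE of a main effect under the stated design and inputs.

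**Conclusion.** The point holds as a misstated precision. On the section's own inputs, the main-effect SE is 0.287; the 0.405 printed under that name is the SE of a single intervention against standard care and is 41% too large for a main effect. The result rests on the implied SD of 1.90, the baseline-adjusted analysis and 40 evaluable women per arm. The factor of √2 between the two SEs needs only the balanced 2x2 layout.

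The practical consequence is uncertainty about the target. If it is the main effects, the trial is better powered than stated: about 98% for 1.14, provided the effects are additive. That condition has to be stated, because the 1.14 derives from studies of a single intervention and is most naturally a simple effect. If the target is each intervention alone against standard care, power is about 80% with no reserve.

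**What to change.** In Sample size calculation, replace the sentence on main-effect precision with one along these lines: SE 0.287 for the main effects (80 vs 80; power about 98% for 1.14, assuming no AIDI-by-CBT interaction) and SE 0.405 for each single intervention against standard care (40 vs 40; power about 80%). Say which of the two is the primary effect.

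In Statistical analysis, or in the analysis plan if that is where it belongs, make sure the regression estimates that effect. With the interaction term included, centred coding (±1/2) returns the main effect and 0/1 coding returns the simple effect.

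Change SD to SE for the 0.405; this is a minor wording correction.

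The cost is a few sentences. No change in sample size is needed.
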